### Objectives

The aim of the present study is to evaluate the effectiveness of a structured group virtual SMS program as an add-on to treatment-as-usual (TAU) in a sample of adults with anxiety disorders. Primary questions: When group SMS is added to TAU in community-based care for patients with anxiety disorders, is the SMS + TAU group more effective in reducing anxiety symptoms than TAU alone? Secondary questions: a) Considering a recovery-oriented approach for patients with anxiety disorders, is there a significant difference between group SMS + TAU and usual care in terms of self-management strategies and personal recovery assessment at the 12-month follow-up? b) Does group SMS + TAU present superior cost-effectiveness and cost-utility, in terms of quality of life and anxiety-free days, than TAU for patients with anxiety disorders at the 12-months follow-up? c) Is there a significant difference between group SMS + TAU and usual care for high-end functioning rates? d) Is there maintenance of gains at 12- and 24-months follow-up? e) Is there differential effectiveness based on moderators (i.e., sociodemographic characteristics, clinical characteristics, past treatment experience) and mediators (i.e., group cohesion, therapeutic alliance, adherence)?

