### Trial design

The trial is a two-arm parallel group multicentre pragmatic superiority randomized controlled trial (RCT), with a 1:1 allocation at the individual level. The group SMS intervention will be offered to participants in the TAU groups after the 12-month follow-up (delayed-intervention). The 24-month follow-up will therefore only provide a within-group dataset. The proposed protocol conforms to SPIRIT guidance [40].

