### Data collection, management, and analysis

#### Participant timeline

The assessments will be conducted at baseline (T_−1_, T_0_), posttreatment (T_1_; 4-month post-randomization) and follow up at 8-month (T_2_), 12-month (T_3_) and 24-month (T_4_) post-randomization. In-treatment assessments for participants and facilitators will also be conducted at sessions 3 and 8. Self-report questionnaires at each assessment period will be completed online through the REDCap application managed at the *Centre de recherche du Centre Hospitalier Universitaire de Sherbrooke* (CRCHUS) at University of Sherbrooke on a secure server with systematic backups. The clinical interviews (T_0_, T_3_, T_4_ only) will be conducted with the Zoom video conferencing service. Data collection with the REDCap application will be managed independently of the treatment assignment. The database will only include coded, depersonalised data, and participant’s identifying information will be stored in a separate secure location with restricted access to the linking code.

We conservatively planned for a 25% attrition at follow up, but we will devote considerable efforts toward a < 5% target with study retention strategies: (1) limiting burden and inconvenience (minimal data collection; web-based; secondary direct data capture through administrative databases); (2) minimal dataset for participants identified at high-risk of attrition (BAI, AQoL-6D); (3) monitoring data collection in real time; (4) education strategies on patient engagement and appreciation (e.g. reminders, website), (5) contact of dropouts; (6) information gathering for relocation; (7) financial compensation (20 $ for each follow up assessment); (8) treatment incentives with delayed-access to SMS for control arm to increase perceived health benefits. Follow up measures at 12- and 24-month are more susceptible to attrition (secondary analysis), and we will include a brief web-based interview that will foster patient engagement. Moreover, we will obtain a complete dataset from provincial administrative data on service utilization.

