#### Sample size

Due to challenges in calculations for mixed regression models [68], we estimated sample size based on the baseline (T_0_) and post-treatment (T_1_) difference between groups for the primary outcome. The sample size was calculated using G*Power with the BAI based on an estimated effect size of the SMS + TAU intervention (Cohen’s *d*) of 0.32 (0.56 intra-group). This corresponds to a 7-point difference based on previous studies [51] that have established *clinically significant change* thresholds for the BAI [69]; such an effect size at post-treatment for symptom reduction is consistent with previous SMS studies for mental disorders [25, 35, 37, 38] as well as with pilot data of SMS (conservative estimates). The 3-point difference and SD for the TAU only group are conservative values based on our current data in a similar study with a TAU group [70]. A sample size of 155 individuals per group is therefore required to detect a 4-point (pooled SD: 12.5) pre-post treatment difference between SMS + TAU and TAU (i.e., a 7-point difference for SMS + TAU and 3-point for TAU) with an 80% power and α = 0.05. As there is a potential for intraclass correlations (ICC) in an individually randomized group treatment trial [71], we also estimated [72, 73] that based on a mixed model accounting for possible between-individual correlations within each intervention group (ICC of 0.02 for based on a similar study [70]), the power would be of at least 76%. With an adjustment for a conservative 25% attrition rate, the proposed sample size is 207 individuals for each treatment arm.

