#### Statistical Analyses

##### Clinical outcomes

Statistical analysis will follow intent-to-treat principles. The primary outcome analysis will be performed at T_1_. The remaining analysis will be conducted considering all measures over time when all participants have completed the 12-month (T_0_ through T_3_) and 24-month follow up (T_0_ through T_4_). Primary question: A mixed model regression with the maximum-likelihood method will be performed to consider between- and within-subject variations in the analysis of the longitudinal effects of SMS + TAU compared to TAU on the primary outcome measure (BAI) at post-treatment (T_1_). To control for potential intra-group variability, random effects will be added on the participants nested in the SMS groups. Baseline clinical variables (e.g., anxiety disorders, comorbid depressive symptoms, psychotropic medication, psychotherapy) will be entered in the model as covariates. Analyses will be conducted with all available data without imputation, as estimation of parameters by maximum likelihood is considered adequate to address missing data as post-treatment in the multilevel model [74, 75].

For secondary questions, logistic regression models will be used to examine high-end functioning rates. The mixed model regression approach will be repeated on all data at the 12-month (T_0_ through T_3_) and 24-month (T_0_ through T_4_) follow-up, and will allow for the inclusion of patients with missing data at any of the follow-up assessments (T_1_,T_2_,T_3_,T_4_). Additionally, treatment effect sizes will be estimated with Cohen’s *d*. We will also conduct hypothesis-generating moderator and mediator analysis [76]. Moderation analyses will be performed for three sets of moderators, including clinical characteristics (e.g., anxiety disorders at baseline, anxiety severity, comorbid depression), previous treatments (psychotropic medication, psychotherapy) and sociodemographic characteristics (e.g., age group, sex, education level). Mediators will be examined for therapeutic alliance, group cohesion and adherence. Sensitivity analysis will be applied to examine the influence of missing data, and to document *per protocol* treatment effects (≥ 8 sessions completed).

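### The SMS + TAU versus TAU mixed model is repeated through 24 months without restriction, although Trial design makes the 24-month data within-group only

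*Protocol article*

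**What the plan says.** Trial design sets out the crossover: "The group SMS intervention will be offered to participants in the TAU groups after the 12-month follow-up (delayed-intervention"). It then states the consequence for the last visit: "The 24-month follow-up will therefore only provide a within-group dataset".

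Statistical Analyses, Clinical outcomes, describes the primary mixed model as an "analysis of the longitudinal effects of SMS + TAU compared to TAU on the primary outcome measure (BAI) at post-treatment (T_1"), and opens with "Statistical analysis will follow intent-to-treat principles". For the secondary questions it continues: "The mixed model regression approach will be repeated on all data at the 12-month (T_0_ through T_3_) and 24-month (T_0_ through T_4_) follow-up". One sentence thus covers both horizons, although T3 precedes the offer of SMS to controls and T4 follows it. The next sentence adds Cohen's d for treatment effects, with no time limit. The section does not mention the delayed intervention.

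The 24-month visit serves secondary question (d) under Objectives: "Is there maintenance of gains at 12- and 24-months follow-up"? Participant timeline gives the visits as "follow up at 8-month (T_2_), 12-month (T_3_) and 24-month (T_4_) post-randomization", with T1 at 4 months.

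**The concern.** Under intention to treat, a control participant stays coded as TAU at T4 whether or not they have by then attended SMS. An arm-by-time term at T4 from the repeated model therefore no longer compares SMS with no SMS. It compares having SMS at the start with being offered it a year later. Maximum likelihood deals with missing values; it does not undo the crossover.

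A contrast of this kind moves towards zero as controls catch up. If it were reported beside the T1 and T3 contrasts, a reader could take the narrowing as loss of benefit when the SMS arm had kept all of its gain. The crossover is planned: Participant timeline lists delayed access for controls among the retention incentives, and the section on assignment of interventions expects control participants' readiness to enrol to be discussed at T3.

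**Working it through.** **Planning figures.** Sample size gives a between-arm difference of 4 points (7 in SMS + TAU, 3 in TAU), SD 12.5, 80% power, α = 0.05, 155 per group and 207 per arm after 25% attrition.

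- Standardised effects: 4/12.5 = 0.32 and 7/12.5 = 0.56, as stated.
- Normal approximation, two-sided: n = 2 × (1.96 + 0.8416)² × 12.5² / 4² = 153.3, so 154 per group. The noncentral t gives 155 (power 0.802 at 155, 0.799 at 154).
- Attrition: 155/0.75 = 206.7, so 207.

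The plan's own figures reproduce, and the point does not depend on any error in them.

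**Expected T4 difference.** Let u be the share of the TAU arm that has taken SMS by T4. Three assumptions are made: the 4-point effect is fully maintained in the SMS arm, crossing controls gain the same 4 points, and u is unknown because the documents do not give it. The expected difference is then

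Δ(T4) = 4 − 4u = 4(1 − u).

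**Benchmark.** For an unadjusted comparison with 155 per arm, SE = 12.5 × √(2/155) = 1.42. The smallest difference reaching p < 0.05 is 1.96 × 1.42 = 2.78 points. Approximate power is Φ(Δ/1.42 − 1.96).

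| TAU uptake u | Expected T4 difference | d | Power |
|---|---|---|---|
| 0 | 4.0 | 0.32 | 80% |
| 0.25 | 3.0 | 0.24 | 56% |
| 0.50 | 2.0 | 0.16 | 29% |
| 0.75 | 1.0 | 0.08 | 10% |
| 1 | 0 | 0 | 5% (the test level) |

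The expected difference falls below 2.78 when u exceeds 1 − 2.78/4 ≈ 0.30. The true loss of benefit in the SMS arm is zero in every row.

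**Earlier contrasts.** The T1 analysis and the T0–T3 model contain no T4 data, so neither is affected. Within the T0–T4 fit, earlier contrasts could be affected only if time enters as a slope. As an illustration, take an unweighted straight line through expected arm differences of 0, 4, 4, 4 and 4(1 − u) at 0, 4, 8, 12 and 24 months. Its slope is 0.113 points per month at u = 0, 0.028 at u = 0.5 and −0.057 at u = 1. On T0–T3 alone the slope is 0.3. The drop from 0.3 to 0.113 comes from the plateau, not from crossover; only the further fall is due to u. With time as a categorical factor this does not arise. The article does not say how time is coded.

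**The case against.** The strongest reply is that the protocol already recognises the problem. Trial design names the delayed intervention and draws the right conclusion from it. A joint mixed model on T0–T4 can supply within-arm time contrasts, so the two sections can be read as compatible. Question (d) names no comparator, whereas (a), (b) and (c) all name the two groups and (a) and (b) are tied to 12 months. Maintenance of gains is most naturally a within-arm question. The choice of contrasts and the coding of time are also matters that a condensed article commonly leaves to the analysis plan.

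Much of this stands. A reader might infer that question (d) will be answered by a between-arm test at T4, and that a maintained benefit will be reported as decay. The document does not say so: no section announces such a test. A reader might also infer that the 24-month data contaminate the earlier between-arm results; the separate T1 and T0–T3 analyses rule that out. The benchmark of 2.78 points is only a rough guide. It uses the sample size planned for T1 and ignores covariate adjustment and clustering. At uptake below about 30% the expected difference stays above it.

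The compatible reading, however, has to be supplied by the reader. Clinical outcomes repeats a comparison of arms, treats T3 and T4 alike, and attaches treatment effect sizes with no limit. Between-arm comparison beyond month 12 is not foreign to the article either: the economic evaluation takes 2-year costs and models cost differences by arm. Analysis plans written from the two sections could specify different T4 analyses. That is a conflict in stated text, not a missing detail.

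**Conclusion.** The point holds as an unreconciled conflict between Trial design and Clinical outcomes, with a conditional consequence. If a T4 between-arm term or Cohen's d is reported from the repeated model, it estimates immediate versus delayed SMS. Its expected size runs from 4 points at no uptake to 0 at full uptake, with nothing lost in the SMS arm. That range rests on the protocol's 4-point effect being fully maintained, on equal benefit in controls who cross over, and on an uptake that the documents do not give. With no uptake there is no distortion.

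The documents do not support saying that the trial has committed itself to a wrong answer to question (d), or that the primary or 12-month results are at risk. This is a secondary 24-month analysis. It is worth correcting because the correction is specific and removes a contrast that could be misread.

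**What to change.** In Statistical Analyses, Clinical outcomes:

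- Limit between-arm inference and between-arm effect sizes to T0–T3.
- For T4, answer question (d) with within-arm change and its confidence interval in the arm randomised to SMS at the start, from T1 to T4 and from T3 to T4. A joint model or an arm-specific model will serve; fitting the SMS arm alone is a preference, not a requirement.
- Report the TAU arm's T3-to-T4 change separately, as before and after delayed SMS.
- If a T4 contrast between arms is shown at all, label it as immediate versus delayed SMS.

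This brings the section into line with what Trial design already says. It is a change of wording only: no new data, visits or participants are needed. It should be settled before the 24-month data are analysed.

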#### Eligibility criteria

This pragmatic RCT focuses on broad inclusion criteria for mixed anxiety disorders groups and minimal exclusion criteria. *Inclusion criteria:* (1) aged 18 and over, (2) fluent in spoken and written French, (3) meeting DSM-5 diagnostic criteria for at least one of the following anxiety disorders: Panic Disorder, Agoraphobia, Generalized Anxiety Disorder, and Social Anxiety Disorder, (4) access to a computer or tablet connected to the internet with microphone and video camera. *Exclusion criteria:* (1) previous enrolment in the SMS intervention for anxiety disorders provided by Relief, (2) active suicidal intentions, (3) severe depressive symptoms (i.e., PHQ-9 score ≥ 20), (4) active substance-related and addictive disorder, and (5) cognitive impairment.

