##### Baseline

Sociodemographic variables will be collected at baseline (T_−1_ et T_0_), and comprise sex and gender, age, marital status, racial identity, ethnicity, education level, income level, occupation, and insurance coverage. We will also collect data on previous experience with mental health services. The web-based screening survey will comprise the Generalised Anxiety Disorder-7 (GAD-7) [45], a 7-item self-report questionnaire measuring anxiety symptomatology. Diagnostic-specific measures will also be administered. The Social Phobia Inventory (SPIN) [46, 47] is a 17-item self-report questionnaire measuring the fear, avoidance, and physiological discomfort associated with social anxiety disorder. Studies have reported good internal reliability, test-retest reliability, and convergent validity [46]. The Panic Disorder Severity Scale Self Report (PDSS-SR) [48] is a questionnaire measuring the severity of seven dimensions of panic disorder. The PDSS-SR shows good internal reliability, test-retest reliability and sensitivity to change [48]. The clinical assessment will be based on the Mini International Neuropsychiatric Interview (MINI) [41], a brief structured diagnostic interview for DSM-5 administered by a trained lay interviewer. Inter-rater reliability will be assessed for 25% of audio-recorded interviews.

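### The exploratory moderator analysis gives age in grouped form; age in years would keep more information for the age part of secondary question (e)

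*Protocol article*

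**What the plan says.** Secondary question (e) in the Objectives asks: "Is there differential effectiveness based on moderators (i.e., sociodemographic characteristics, clinical characteristics, past treatment experience) and mediators". It does not single out age.

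Statistical Analyses, Clinical outcomes, describes the analysis that answers it. Its status is exploratory: "We will also conduct hypothesis-generating moderator and mediator analysis". Its scope is broad: "Moderation analyses will be performed for three sets of moderators". The third set is illustrated as "sociodemographic characteristics (e.g., age group, sex, education level", which is the only place where the article says in what form age would be a moderator. No number of groups and no cut-points are given.

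On the data side, the Baseline section lists the sociodemographic variables, which "comprise sex and gender, age, marital status, racial identity" and others. The list says age, not age band. Eligibility requires participants to be "aged 18 and over", with no upper limit.

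**The concern.** A treatment-by-age-group interaction assumes that the benefit of SMS is constant within each band and jumps at each boundary. If moderation by age is closer to a smooth trend, differences within bands are thrown away. With three or more bands, the overall interaction test also spends extra degrees of freedom on a pattern that one slope would describe.

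Interaction tests in a trial sized for a main effect are weak to begin with, and the Discussion says that these analyses should inform future trials. Losing information that has already been collected makes the age finding less precise at no saving. The stake is confined to one moderator.

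**Working it through.** **The plan's own figure.** Inputs from Sample size: 4-point difference, pooled SD 12.5, 80% power, α = 0.05 (two-sided reproduces the result). n = 2 × (1.96 + 0.8416)² × 12.5² / 4² = 153.3, so 154 per group. The t-test version gives 154.3, rounded up to the stated 155. With 25% attrition, 155 / 0.75 = 206.7, so 207 per arm, as stated. The article gives no figure for the moderator analysis, so everything below rests on stated assumptions.

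**Assumptions.** N = 2 × 155 = 310 analysed, 1:1 allocation, residual SD 12.5, moderation linear in age, clustering ignored. The age distribution is not given; normal and uniform are used as a range. The number of groups is not given; two, three and four equal-sized groups are used.

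**Information kept by grouping.** For a linear effect this is the squared correlation between age and its group means, Σ pⱼmⱼ² / Var(age), where pⱼ is the share of participants in group j and mⱼ the group's mean age, measured from the overall mean.
- Normal age: two groups 2/π = 0.637; three 0.793; four 0.861.
- Uniform age: 1 − 1/g² for g groups, so 0.75, 0.889 and 0.938.

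**Precision of the interaction.** With treatment coded 0/1 and age in SD units, SE = 2 × 12.5 / √310 = 1.42 BAI points per SD of age. The slope detectable with 80% power is (1.96 + 0.8416) × 1.42 = 3.98 points per SD.

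**Power.** The noncentrality for a slope of b points per SD is b² × 310 / (4 × 12.5²) = b² × 0.496, which is 1.98, 4.46 and 7.94 for b = 2, 3 and 4. Grouping multiplies it by the share kept, and g groups are tested on g − 1 degrees of freedom.

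| Coding of age | 2 points per SD | 3 points per SD | 4 points per SD |
|---|---|---|---|
| Continuous | 29% | 56% | 80% |
| Two groups, median split | 20-23% | 39-45% | 61-68% |
| Three equal groups (2 df) | 19-20% | 37-41% | 61-66% |
| Four equal groups (3 df) | 17-18% | 35-37% | 58-62% |

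Ranges run from normal to uniform age. As a hand check, the median split with normal age at 4 points gives √(7.94 × 0.637) = 2.25 and Φ(2.25 − 1.96) = 61%.

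**Where the loss comes from.** With three or four groups, much of it is the extra degrees of freedom. If the groups were instead scored by their means and tested as a 1-df trend, power at 4 points would be 71-76% with three groups and 74-78% with four.

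**The case against.** The strongest reply is that age group is one item in a list of examples. A reader might infer that the plan commits to analysing age only in bands, but the article does not say so. It gives no model form for this moderator, and an unseen analysis plan may use age in years. That limits the point to the form the article happens to name; it does not remove it, because no other form is given.

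Second, the analysis is declared hypothesis-generating and no power is claimed for it, so low power breaks no promise. That stands. It sets the weight of the point, but it is no reason to prefer the less informative coding.

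Third, the larger assumed interactions are demanding. Four points per SD of age equals the whole planned treatment effect: it would mean no benefit one SD from the mean age on one side and double the benefit on the other. At 2 points per SD the test is weak under either coding. That also stands, and it is why a range is shown.

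Fourth, the loss is conditional. If moderation is step-like or non-monotone, bands can do as well as a straight line or better. A spline check answers much of this, though not all.

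Two further inferences are tempting and unsupported. One is that the cut-points will be chosen after the results are seen: their absence is detail that an article may leave to the analysis plan. The other is that anxiety severity will be banded as well: the article lists it as a moderator without saying so, and the BAI bands under Primary outcome measure only describe the scale.

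**Conclusion.** The point holds as a minor efficiency improvement. The form named for age is less informative than the recorded variable if moderation by age is roughly smooth. Under the assumptions above, equal groups give up between about 6% (four groups, uniform age) and 36% (median split, normal age) of the information. Where continuous age would have 80% power, grouped age would have about 58-68%.

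A reader might conclude that secondary question (e) as a whole is compromised. It is not: the question spans three classes of moderators plus mediators, and only its age component is affected. Age grouping plays no part in the stated sample size or the T₁ primary analysis, so the primary result and its error rate do not change. The exact loss cannot be fixed from the article, because it gives no age distribution, grouping or interaction size.

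**What to change.** In Statistical Analyses, Clinical outcomes, replace age group by age in years in the list of sociodemographic moderators. State that moderation by age is tested as a treatment-by-continuous-age interaction, with a spline as a check for non-linearity, and that age bands serve only to display the fitted effect.

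The cost is one phrase and a short sentence. No new data are needed, provided age is captured in years, as the Baseline list suggests but does not spell out. The primary analysis and the sample size stay as they are.

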**Discussion:**

This study will contribute to the limited knowledge base regarding the effectiveness of structured group self-management support for anxiety disorders. It is expected that changes in patients’ self-management behaviour will lead to better anxiety management and, consequently, to improved patient outcomes.

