**RECOVERY-FOCUSED OUTCOMES**							
Recovery Assessment Scale - Revised		X		X		X	X
Mental Health Self-Management Questionnaire		X		X		X	X

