##### Questionnaires completed during SMS sessions

The appreciation of the alliance for both participants and facilitators will be assessed with the 12-item version of the Working Alliance Inventory (WAI) [60, 61]. The WAI shows good construct validity and high internal consistency [62]. The perceived cohesiveness and bond for participants will be examined with the 9-item Gross Cohesion Scale (GCS) [63], a scale with acceptable reliability and validity. These measures will be used at sessions 3 and 8.

A logbook will also be used by facilitators to record intervention adherence for each participant as well as to report experiences and perceptions related to SMS group facilitation. The logbook content will provide a better understanding of the actual implementation of the program. The facilitators will also complete a brief questionnaire comprising sociodemographic questions, items on academic and professional backgrounds, as well as experience with SMS, group interventions and anxiety disorders.

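### Alliance and cohesion are named as mediators but exist only in the SMS arm, so they cannot mediate the randomised effect; adherence supports at most a dose analysis

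*Protocol article*

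**What the plan says.** The protocol article names the mediators twice. Secondary question (e) under Objectives gives a closed list: "mediators (i.e., group cohesion, therapeutic alliance, adherence". The Clinical outcomes section repeats it: "Mediators will be examined for therapeutic alliance, group cohesion and adherence". The same section sets the status of the work: "We will also conduct hypothesis-generating moderator and mediator analysis".

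The section headed "Questionnaires completed during SMS sessions" describes the Working Alliance Inventory and the cohesion scale and fixes their timing: "These measures will be used at sessions 3 and 8". For adherence it says: "A logbook will also be used by facilitators to record intervention adherence for each participant". Table 2 files all three as process measures and marks them in the Intervention column only, never at T0 to T4. Under Trial design, the control arm is offered the programme only after the 12-month follow-up, and the 24-month data are within-group.

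On mechanism, the Abstract (and the Background in similar words) expects that changes in patients' "self-management behaviour will lead to better anxiety management and, consequently, to improved patient outcomes". The "Mental Health Self-Management Questionnaire" (MHSQ) measures use of such strategies. Table 2 schedules it at T0, T1, T3 and T4 with no restriction by arm. It is analysed as an outcome and does not appear among the mediators.

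**The concern.** A mediator of a randomised treatment effect needs a value in both arms. The indirect effect combines the effect of allocation on the mediator with the effect of the mediator on the outcome. Alliance with an SMS facilitator and cohesion of an SMS group have no counterpart in TAU, so the first of these paths does not exist.

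What can be computed is the association, among SMS patients, between their ratings and their later anxiety. That association is observational: patients who engage well may also be those who would have improved anyway. For the two scales it is further limited to patients who complete them at sessions 3 and 8. If it is reported as mediation, readers may take it for an explanation of the randomised effect, which the design cannot give. A measure of the pathway the protocol expects is meanwhile scheduled in both arms and is not used for this purpose.

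**Working it through.** **Inputs.** From Sample size: a 4-point difference, SD 12.5, 80% power, α = 0.05 (two-sided assumed), 155 per arm, 25% attrition, 207 per arm. The article gives no figure for the mediation analysis.

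**The plan's own figure.** n per arm = 2 × (1.96 + 0.8416)² × (12.5/4)² = 2 × 7.849 × 9.766 ≈ 153.3, so 154. The t-test version gives 154.3, so 155. Attrition: 155/0.75 = 206.7, so 207. These reproduce.

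**Where each variable has a value before 12 months.**

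| Variable | SMS + TAU | TAU |
|---|---|---|
| Alliance | sessions 3 and 8 | none |
| Cohesion | sessions 3 and 8 | none |
| Adherence | logbook, each participant | 0 by design |
| MHSQ | T0, T1, T3 | T0, T1, T3 |
| BAI | T0, T1, T2, T3 | T0, T1, T2, T3 |

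**Check 1: mediator missing in TAU.** The article does not specify a mediation model, so I take the simplest, BAI = β0 + β1·arm + b·M. Patients with M observed all have arm = 1, so the arm column equals the intercept column. The design matrix has rank 2 of 3, and only the SMS completers (155) contribute. Nothing estimates the effect of arm on M.

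**Check 2: mediator filled in as a constant c in TAU.** The model can now be fitted. M does not vary in TAU, however, so b comes from the SMS arm alone; in 2,000 simulated trials the pooled and SMS-only slopes agreed to about 10⁻¹⁴. The indirect effect is b × (mean of M in SMS − c), so its size depends on the chosen c.

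**Illustration, with assumed values.** Let an unmeasured standard normal trait U raise alliance (M = 5 + 0.6U + noise of SD 0.8, so the variance of M is 0.36 + 0.64 = 1) and lower BAI by 4 points per unit. Let M have no effect on BAI and the arm effect be −4.
- Expected slope: b = 0.6 × (−4)/1 = −2.4. Simulated mean: −2.36.
- With c = 0: indirect effect −2.36 × 5 = −11.8, direct effect −4 + 11.8 = +7.8. The truth is 0 and −4.
- With c = 3: indirect effect −2.36 × 2 = −4.7.
- With c = 5: indirect effect 0.

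These sizes follow from the assumptions and are not forecasts for this trial. The lack of identification does not depend on them.

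**Check 3: what stays estimable within SMS.** Detectable correlation at 80% power = tanh(2.8016/√(n − 3)). This gives 0.22 for n = 155 and 0.19 for n = 207, ignoring clustering by SMS group.

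**Check 4: adherence.** Sessions attended has a randomised contrast, with zero in TAU. It could enter an instrumental-variable or complier analysis that assumes allocation affects BAI only through attendance. That estimates the effect of receiving the programme, not the share of the effect passing through a mediator. TAU adds no variation, so the slope problem in Check 2 applies here too.

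**The case against.** The strongest defence is that little rests on this. The article calls the analysis hypothesis-generating, and the Discussion repeats that it serves future trials. Table 2 already files the three variables as process measures, and the Interventions section speaks of process-outcome correlation for the integrity data. This limits the weight of the point. It does not make the indirect effect estimable. A fuller analysis plan could not create TAU values for alliance or cohesion, so it could cure the problem only by departing from the named list.

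Four stronger readings are tempting, and the documents do not support them.
- A reader might infer that all three variables are undefined in half the sample. That holds for alliance and cohesion only. Adherence is zero in TAU and is logged for every SMS participant, so it is also not confined to those present at sessions 3 and 8.
- A reader might infer that question (e) cannot be answered. Its moderator part is unaffected.
- A reader might infer that the expected mechanism goes untested. Question (a) already compares self-management between arms, and the primary question tests anxiety. Only the formal indirect effect is absent. The mechanism is stated as an expectation, and no mediation test through MHSQ is promised, so its absence contradicts nothing.
- A reader might infer that the correlations will be presented as mechanisms. The article does not say so.

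A fair objection also applies to the remedy. MHSQ at T1 is measured together with BAI at T1, and patients at high risk of attrition may be asked for BAI and AQoL-6D only. Both difficulties stand and are taken up in the fix.

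**Conclusion.** The point holds for alliance and cohesion. Mediation of the randomised SMS + TAU versus TAU effect through them cannot be estimated at any sample size, because they have no value in the 207 planned TAU participants during the comparison. What remains is an association within the SMS arm. Adherence supports at most a dose or complier-type analysis, assuming that TAU patients do not obtain the programme elsewhere before 12 months and that the exclusion restriction holds.

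The weight is minor to moderate. The fault lies in a secondary, exploratory analysis, and the primary T1 analysis, the sample size and the moderator analyses stand. It deserves correction because the text fixes the wrong variables in two places and the correction is cheap. The MHSQ analysis is a recommendation and does not repair a broken promise.

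**What to change.** 1. In Objectives (e) and Clinical outcomes, relabel alliance, cohesion and adherence as process predictors of outcome within the SMS arm, with no mediation claim. If an effect of attendance is wanted, specify it separately as a complier-type analysis and state the exclusion restriction.

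2. For the mediator question, specify arm → MHSQ at T1 (adjusted for T0 MHSQ) → BAI at T2 or T3 (adjusted for T0 BAI), kept hypothesis-generating. Both arms contribute, the first path is a randomised comparison, and the mediator precedes the outcome.

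3. Treat T1 BAI as a mediator-outcome confounder that is itself affected by treatment. Adjusting for T0 values alone does not deal with it, and simply adding it as a covariate may block part of the effect. Use a method suited to such confounders, for example an interventional indirect effect, and show results with and without T1 BAI. Add a sensitivity analysis for unmeasured mediator-outcome confounding.

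4. Report MHSQ missingness by arm and by use of the minimal dataset described under Participant timeline, and examine how far selective gaps could change the result.

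5. State that the analysis concerns later BAI and does not explain the primary effect at T1. Use the recovery scale (RAS-r) as a second mediator only with caution, if at all: its domain on not being dominated by symptoms may overlap with the outcome.

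The cost is a change of wording and one added analysis on measures already scheduled, with no new visits. The downside is that the result rests on confounding assumptions that the data cannot test.
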